##### Sensitivity analyses

The results obtained by using a mixed effects model of the (log-transformed) endpoint UACR with the allocated grouping structure as the exposure, a random effect term to account for the study centre variability, only incorporating (log-transformed) baseline UACR as a covariate without additional baseline covariates will also be made available. In addition, the sensitivity of the results to the decisions made in constructing the imputation model, will be investigated using visualisations of the distributions of imputed and observed values, standard regression diagnostics [17], and comparisons with complete case analysis. The results will be presented as outlined in Fig. 2.

**Fig. 2 Fig2:**
[figure not shown]
Forest plot of the mean differences (95% confidence intervals) in the endpoint urine albumin–creatine ratio (UACR) (intervention versus placebo group)

##### Additional analyses

Supplementary analyses will be completed by repeating the main analysis described in “Main analysis model” section - “Sensitivity analyses” section using (1) the modified ITT and (2) the PP analysis sets, and these results will be reported in the proposed format.

#### Secondary analyses

The analyses described in “Main analysis model” section - “Additional analyses” section will be repeated:
For the secondary outcome measures defined in “Secondary outcome measures” section, andUsing the subsets of the GKT137831 group who have taken the 800 mg/day drug for (a) > 6 months and (b) > 12 months as the intervention group for all primary and secondary outcomes defined in “Primary outcome measure” section and “Secondary outcome measures” section, respectively.

The results will be reported in the proposed format.

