## Study methods

### Trial design

This is a multicentre, multi-national, phase 2, randomised, double-blind, placebo-controlled clinical trial with two parallel arms with 1:1 allocation ratio, which will test the effect of oral GKT137831 400 mg taken twice a day compared to placebo, on urine albumin to creatinine ratio, in adults with type 1 diabetes mellitus and persistent albuminuria despite optimal preceding standard of care treatment. The trial started recruitment in December 2017 and the recruitment is expected to end on 30 June 2020. The treatment period is 48 weeks with total study duration for the participant of up to 56 weeks. Figure 1 and Table 4 of the protocol [2] describe, respectively, the timeline for the study, which consists of 10 study visits in total, and the schedule of events.

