#### Main analysis set (ITT analysis set)

The ITT analysis set is the main analysis set that will be used for evaluating the primary hypothesis, and it consists of all randomised participants with each participant retaining their treatment group as originally allocated by the randomisation procedure.

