##### Midpoint urine albumin–creatinine ratio

The urinary albumin excretion level at the midpoint of the treatment period measured by the urine albumin–creatinine ratio (midpoint UACR), defined as the geometric mean of the two consecutive, daily, first void UACR values taken at the midpoint of treatment at 24 weeks of treatment.

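### The > 12-month subset cannot exist in a 48-week treatment period, and the > 6-month subset filters only the active arm on post-randomisation exposure, including for outcomes measured at week 24

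*SAP article*

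**What the plan says.** The Trial design section gives one active regimen, "oral GKT137831 400 mg taken twice a day compared to placebo", in "two parallel arms with 1:1 allocation ratio". On duration it says: "The treatment period is 48 weeks with total study duration for the participant of up to 56 weeks". Timing of final analysis places the analysis of all outcomes at 48 weeks, and the last UACR samples for the primary outcome are taken then.

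Secondary analyses then repeats everything from the main model through the additional analyses, this time on "the subsets of the GKT137831 group who have taken the 800 mg/day drug for (a) > 6 months and (b) > 12 months". Each restricted group stands in for the full active arm, and this applies to every primary and every secondary outcome. The additional analyses are those "using (1) the modified ITT and (2) the PP analysis sets", so each subset is to be run under ITT, modified ITT and PP. No duration rule is stated for placebo.

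The ITT set is defined so that "it consists of all randomised participants with each participant retaining their treatment group as originally allocated by the randomisation procedure". The midpoint UACR samples are "taken at the midpoint of treatment at 24 weeks of treatment", and midpoint eGFR is also a week-24 value. Confidence intervals and significance level makes the tests of primary and secondary hypotheses one-sided at 5%, with Benjamini-Hochberg adjustment for the secondary ones.

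**The concern.** There are three separate problems.

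1. **Subset (b) contradicts the schedule.** A plan written to limit reporting bias should not prespecify an analysis that nobody can enter. It leaves a threshold that someone may reinterpret once results are known. With 4 outcomes (one primary, three secondary) and 3 analysis sets, it accounts for 4 x 3 = 12 main-model fits with no one in the intervention group.

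2. **Subset (a) is selected on what happens after randomisation, in one arm.** Withdrawals/follow up provides for participants who stop the intervention but stay in follow-up, so endpoint values from early stoppers may exist. They would be discarded on active and kept on placebo. An analysis filtered this way is not ITT as the SAP defines it.

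3. **For the week-24 outcomes the selection comes after the outcome.** Nobody can have more than 6 months of exposure at week 24, so membership depends on later events, possibly including reactions to the week-24 result.

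These analyses sit under the secondary heading, are to be reported in the proposed format, and carry one-sided p values. Benjamini-Hochberg adjustment addresses multiplicity; it does nothing about selection.

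**Working it through.** The SAP gives no figure for these subset analyses. Its power statement concerns the main comparison and is not used here.

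**Durations** (one month = 365.25/12 = 30.44 days)
- Treatment: 48 x 7 = 336 days; 336/30.44 = 11.04 months.
- Twelve months: 365.25/7 = 52.2 weeks, which is 365.25 - 336 = 29 days beyond the full course.
- With 4-week months: 48/4 = 12 exactly, still not more than 12.
- Total study time: 56 x 7/30.44 = 12.9 months, but this includes time off treatment, such as the 2 weeks before randomisation when baseline samples are taken.
- Six months: 182.6/7 = 26.1 weeks. The midpoint visit is at 24 x 7/30.44 = 5.5 months.

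**Who is compared with whom in subset (a)**
- ITT repeat: filtered active arm against all randomised placebo.
- Modified ITT repeat: the same, except for placebo participants who took no capsule.
- PP repeat: both arms are limited to 48-week completers without an important deviation, so (a) is close to the ordinary PP active arm and the asymmetry largely goes.

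**Illustration of size under no drug effect.** These inputs are assumptions, not SAP figures:
- 71 per arm (142/2, reading 142 as the total randomised);
- log SD 0.5;
- a proportion d = 10-20% stopping by 6 months in each arm;
- correlation r = 0.3-0.5 between the tendency to stop and a worse endpoint, to be read as what remains after baseline adjustment;
- a share s of placebo stoppers who supply an endpoint.

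Let z be the 1 - d normal quantile and f its normal density. In SD units:
- bias b = -r f/(1 - d) + r f (1 - s)/(1 - d + s d)
- SE = sqrt(1/n_a + 1/n_p), with n_a = 71(1 - d) and n_p = 71(1 - d + s d)
- one-sided error = Phi(-1.645 - b/SE)

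Worked case, d = 0.10, r = 0.3, s = 1: f = 0.1755; b = -0.3 x 0.1755/0.9 = -0.0585; SE = sqrt(1/63.9 + 1/71) = 0.1724; error = Phi(-1.645 + 0.339) = 9.6%.

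Worked case, d = 0.20, r = 0.5, s = 1: f = 0.2800; b = -0.5 x 0.2800/0.8 = -0.175; SE = sqrt(1/56.8 + 1/71) = 0.178; error = Phi(-1.645 + 0.983) = 25.4%.

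| Placebo stoppers with endpoint | Bias, log units (0.5 x b) | One-sided error, formula | One-sided error, simulation |
|---|---|---|---|
| All | -0.029 to -0.087 | 9.6-25.4% | 9.7-25.8% |
| Half | -0.015 to -0.049 | 7.1-13.3% | 6.8-13.5% |
| None | 0 | 5% | about 5% |

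Each row spans (d, r) from (0.10, 0.3) to (0.20, 0.5). The simulation used 20,000 trials per setting. The log SD scales the bias but does not affect the error rate.

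With the sign reversed (r = -0.3, s = 1), the bias is +0.029 to +0.053 against the drug and the rejection rate is about 1-2%.

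**The case against.** The best defence is that these are supplementary on-treatment analyses in a phase 2 trial, and that the main ITT analyses of primary and secondary outcomes do not depend on them. That stands, and it limits the severity.

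A reader might infer that subset (a) systematically favours the drug. The documents do not support that: the direction depends on whether stoppers have worse or better UACR, and the SAP says nothing about this.

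A reader might also take the 10-26% range as the expected error rate. It requires every placebo stopper to supply an endpoint. Participants who leave follow-up have no week 46/48 value. Missing data methods does not impute when only the outcome is missing, although it allows item-level imputation for the composite UACR. The share who stop drug but stay in follow-up is not given. The 20% stopping rate is also high against the plan's own expectation: if 142 is the total randomised and 120 complete, loss over the whole 48 weeks is 22/142 = 15.5%. The rates above are for unadjusted tests.

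On subset (b), visit windows are in the protocol, which is not shown. A participant would need about 29 extra days of dosing to exceed 12 calendar months. If 4-week months were meant, a few late visits could qualify by accident, but that is not a meaningful subset. The 56-week figure does not help, because it is study time and not treatment time.

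**Conclusion.** The point holds in three parts. Subset (b) is empty under the stated 48-week schedule. This rests on arithmetic alone. Subset (a) is not a randomised comparison in the ITT and modified ITT repeats, and its bias has unknown sign and size. The illustrative one-sided error runs from the nominal 5% to about 26% if stoppers have worse UACR, and falls to about 1-2% in the reversed case, all on assumed inputs. Applying (a) to week-24 outcomes conditions on exposure that occurs after the measurement, whatever those inputs are.

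The stronger inference, that the trial's efficacy conclusion is compromised, does not follow, because the primary ITT analysis is untouched. This should be fixed, but it is not a condition for the main analysis to be valid.

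**What to change.** Before unblinding:

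1. Reconcile Secondary analyses with Trial design: either delete subset (b) or restate its threshold as one that 48 weeks of treatment can contain.
2. For subset (a), apply the same rule, duration of study capsules taken, to both arms.
3. Restrict (a) to the week 46/48 outcomes (endpoint UACR and endpoint eGFR).
4. Label it a non-randomised supplementary on-treatment analysis, report an estimate and interval without a confirmatory p value, and do not call any version of it ITT.

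A complier-average estimate with allocation as instrument could be added, but it is not a clean replacement. Using more than 6 months as the compliance indicator assumes that shorter exposure has no effect (the exclusion restriction). A partial effect in early stoppers would inflate the estimate. If it is used, the SAP should state both points.

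The cost is SAP wording only. The downside is slightly fewer placebo participants in this supplementary analysis. A common rule removes the one-sided filter but does not restore randomisation, which is why the label is needed.

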#### Exploratory analyses

The distributions of the exploratory measures mentioned in “Exploratory outcome measures” section will first be inspected, and then suitably transformed. To inspect high-dimensional data, relative log abundance/expression plots [18] and loadings/scores plots obtained from principal component analyses will be used [19]. “Remove unwanted variation” (RUV) [20] normalisation methods will be used to either remove or accommodate unwanted variation in the high-dimensional data as appropriate. Systematic patterns in the data will be investigated using clustering techniques such as the hierarchical cluster analysis coupled with inspection of heatmaps. Depending on the distribution of the exploratory outcome measure, the differences in the change in the exploratory outcome measure from baseline to endpoint between the intervention and placebo groups will be examined using either linear or generalised linear regression models. In these models, the endpoint exploratory measure will be used as the outcome and a categorical variable indicating the allocated grouping structure (intervention versus placebo) will be used as the exposure, incorporating exploratory measure at baseline and other confounding variables as covariates. Testing for multiple comparisons in high-dimensional data will be accounted for, by adjusting the *p* values obtained from these analyses using the Benjamini-Hochberg method to address the false discovery rate [5]. The exploratory findings from these analyses will inform further directions.

#### Safety analyses

Safety analyses will be based on the safety analysis set described in “Safety analysis set” section. The safety outcomes presented in Supplementary Table 2 will be summarised by group (intervention and placebo). Categorical variables will be summarised using frequencies and percentages, and the continuous variables will be summarised using appropriate central tendency and dispersion measures, and presented either as mean and standard deviation (SD) or median and 25th–75th percentile. Percentage standardized differences between the two groups will be calculated for all variables. A value ≥ 10% difference will be taken as a meaningful difference between the groups. In addition, where possible, a linear mixed model or a generalised linear mixed model will be used with the safety measure at the end of the trial as the outcome, a categorical variable indicating the group structure (intervention or placebo group) as the exposure, and the safety measure at the beginning of the trial as a covariate, also accounting for centre variability. Where appropriate, an estimate of the group effect, 95% confidence interval and *p* value will be presented. The results will be summarised in Table 5.

**Table 5 Tab5:** Safety analyses results using the safety analysis set

Safety outcome measure	Values		Percentage standardized difference	Estimated difference^a^	95% Confidence Interval^a^	*P* value^a^
	Intervention (GKT137831) group (*n* = xxx)	Placebo group (*n* = xxx)				
Treatment-emergent adverse events, *n* (%)						
Abnormal laboratory analytes, *n* (%)						
Abnormal physical examination and vital signs, *n* (%)						
QT corrected electrocardiogram (ECG), mean (SD)						
Treatment-emergent qualitative ECG, *n* (%)						
Concomitant medications, *n* (%)						
Systolic blood pressure (mmHg), mean (SD)						
Diastolic blood pressure (mmHg), mean (SD)						
Heart rate (beats per minute), mean (SD)						
Weight (Kg), mean (SD)						

*SD* standard deviation

^a^ If feasible to carry out testing; in the intervention group compared to the placebo group

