### Sample size

Up to 284 participants in total are expected to be screened (anticipated screen fail rate up to 50%) with 142 participants each randomised to the treatment and placebo groups, to achieve 120 participants reaching the end of the treatment period in total (60 per treatment group). Sect. 2.5 of the protocol [2] provides details of the sample size calculations. In brief, the assumptions of the sample size calculations were the following: mean UACR of 13.56 mg/mmol in the control arm, difference between UACR means in the treatment arm of 3.56 mg/mmol/L (26% reduction in mean UACR in the treatment arm), equal standard deviations of 7.5 mg/mmol in the two arms, and within-subject correlation of 0.3. Using mixed model analysis of covariance with log-transformed UACR as the outcome, several scenarios were examined: 60 participants per treatment arm are required to achieve power > 90% with an alpha level of 0.05 and two-sided hypothesis testing, and 40 participants per treatment arm are required to achieve power > 90% with an alpha level of 0.05 and one-sided hypothesis testing.

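### At this trial's size, the 10% standardised-difference rule for safety outcomes would label chance differences as meaningful more often than not

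*SAP article*

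**What the plan says.** The *Safety analyses* section of the SAP summarises the safety outcomes by arm and then states: "Percentage standardized differences between the two groups will be calculated for all variables". The next sentence sets the criterion: a value of 10% or more "will be taken as a meaningful difference between the groups". It gives no reason for 10%, no minimum event count and no allowance for sample size.

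A model comes on top of this: "In addition, where possible, a linear mixed model or a generalised linear mixed model will be used". An estimate, 95% interval and p value follow where appropriate. Table 5 has ten rows and prints the standardised difference beside these model results, with a footnote that testing depends on feasibility. *Confidence intervals and significance level* makes the safety tests two-sided at 5%.

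The 10% figure also appears under *Covariate adjustment*, where it selects baseline variables as extra covariates. There the SAP says that the magnitude is meant; *Safety analyses* does not.

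**The concern.** A 10% standardised difference can serve as a descriptive screen for baseline balance. *Safety analyses* turns it into a finding about outcomes after randomisation, where the question is whether the drug did something. The rule looks neither at the precision of the difference nor at its clinical importance. With small arms, a difference of a tenth of a standard deviation is well inside sampling noise.

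Safety is a stated objective of this phase 2 trial, and the conclusion of the SAP says that the results may inform phase 3 trials. If the rule is followed, the report will describe several outcomes as meaningfully different when nothing but chance need be at work. The plan gives the reader no way to reconcile that label with a non-significant model result in the same row.

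**Working it through.** **Inputs.** From *Sample size*:
- 120 participants in total, 60 per arm, are expected to reach the end of treatment.
- Up to 284 are to be screened, with up to 50% failing: 284 × 0.5 = 142 randomised, or 142 / 2 = 71 per arm. The SAP does not state 71; it is inferred.
- The text also has "142 participants each randomised to the treatment and placebo groups". Taken literally, that is 142 per arm, which cannot be squared with 284 screened and half of them failing. It serves as an upper bound.

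Allocation is 1:1. The safety set requires a dose and a later assessment, so it is at most the number randomised.

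**The plan's own figure.** The SAP gives no error rate for the 10% rule. Its sample size does reproduce. Means of 13.56 and 10.00 with SD 7.5 convert, under a lognormal model, to log SDs of 0.517 and 0.668 (pooled 0.597) and a log-mean difference of 0.394. Power is then 95.1% at 60 per arm two-sided and 90.4% at 40 per arm one-sided, both above 90% as stated.

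**Continuous outcomes, no true difference.** With n per arm, the standardised difference d is approximately normal with mean 0 and SE = √(2/n). The chance of crossing is 2 × [1 − Φ(0.10 / SE)].

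**One event against none.** The difference in proportions is 1/n and the averaged variance is (n − 1)/(2n²), so d = √(2/(n − 1)).

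| Per arm | SE of d | 0.10 in SEs | Chance of crossing 10% | 1 event v 0 |
|---|---|---|---|---|
| 60 | 18.3% | 0.55 | 58.4% | 18.4% |
| 71 | 16.8% | 0.60 | 55.1% | 16.9% |
| 142 | 11.9% | 0.84 | 39.9% | 11.9% |

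The chance falls below 50% only above about 91 per arm and reaches 5% only at about 768 per arm (2 × (1.96/0.10)² = 768). One event against none is flagged up to 201 per arm.

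**Binary outcomes.** Exact enumeration of two binomial arms with equal true rates between 1% and 90% gives a chance of 57–68% at 60 per arm and 51–58% at 71. At a true rate of 0.5% it is 40% and 42%, because both arms often have no event.

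**Against the p value.** In a simple unadjusted comparison, a row exactly at 10% has a two-sided p of about 0.58 at 60 per arm and 0.55 at 71. Reaching p = 0.05 takes 1.96 × SE: about 36% at 60 per arm and 33% at 71. Rows between 10% and roughly 33–36% would therefore be meaningful by the rule and non-significant by such a test.

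**Over Table 5.** If the continuous-outcome chance applied to all ten rows, the expected number flagged by chance would be 10 × 0.551 = 5.5 to 10 × 0.584 = 5.8, or 10 × 0.399 = 4.0 at 142 per arm. This expectation does not need independent rows.

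**The case against.** The strongest reply is that the flag does not stand alone. Table 5 also carries an estimate, a 95% interval and a p value where feasible, so precision is not missing from the safety analysis as a whole. Some clinical judgement may already enter through the protocol's definition of abnormal laboratory values, which is not shown. No stopping rule or primary inference depends on the flag. All of this stands and limits the consequence. It does not rescue the rule, because the models are conditional and nothing says that they override the label.

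The sample size is also an inference. At a literal 142 per arm, the chance for a continuous outcome is about 40%, not more than half. If only one direction counted, it would be about 28–29% at 60 to 71 per arm.

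A reader might infer more than the SAP supports:
- *That every row has the same 55% chance, so a table with no flags is almost impossible.* Rows differ. The concomitant-medication row, for instance, might be 100% in both arms, since participants must already be on standard therapy. The blood pressure, heart rate and vital-sign rows are likely to be correlated, so multiplying their chances is not justified. One event against none is also unlikely in rows that pool many events.
- *That the rule flags one against none yet passes two against one.* For two against one, d = √(2/(3n − 5)), which is 9.8% at 71 per arm but 10.7% at 60. The contrast reverses at 68 per arm or fewer.
- *That early stoppers drop out of the models,* because these are fitted "with the safety measure at the end of the trial as the outcome". *Withdrawals/follow up* provides for people who stop treatment but stay in follow-up, and they can supply an end value. Early events can still appear in the treatment-emergent counts. Whether a repeated-measures or worst-value model would be better is a separate preference that depends on a visit schedule not shown.
- *That real signals would be hidden.* An over-sensitive flag removes no row from the table.

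**Conclusion.** The rule is wrong as written. At 60 to 71 per arm the threshold is only 0.55 to 0.60 standard errors, so with no drug effect a continuous safety outcome is called meaningful about 55–58% of the time. Binary outcomes have a similar rate unless events are very rare. One event against none is enough at every sample size that the document could mean. About half of the Table 5 rows could be so labelled by chance, and the plan does not say whether the label or the model result governs.

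These figures assume that 71 per arm is the right reading of the screening numbers, that the magnitude of the difference is meant (as under *Covariate adjustment*), and that d is approximately normal for continuous outcomes. The literal 142 per arm lowers the chance to about 40%, which is still far too high for a criterion of meaningful difference. What is affected is the interpretation of safety; the primary efficacy conclusion is not.

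**What to change.** In *Safety analyses*, delete the sentence that makes 10% the criterion for a meaningful difference. The standardised difference may stay in Table 5 as a descriptive column, with no threshold attached.

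Base interpretation on risk differences with exact or score 95% intervals for event rows, and on mean differences with 95% intervals for continuous rows. Read both together with the protocol's own definitions of abnormal values.

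The cost is SAP wording and small changes to Table 5. No new data are needed: the same counts and means that the section already summarises are used.

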### Safety analysis set

The safety analysis set consists of all participants who have taken at least one capsule of investigational product or placebo and have at least one subsequent safety assessment, which is described in Sect. 4.2 of the protocol [2].

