#### Safety outcome measures

The key safety outcome measures are treatment-emergent adverse events and abnormal laboratory analytes as defined in the protocol [1] Sect. 10.4.4.2 and 10.4.4.3, respectively. All safety outcome measures are given in Supplementary Table 2 along with references to the sections where they are defined in the protocol [1].

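### The supplementary between-arm safety model uses only the end-of-trial value, so it omits safety-set members without one and ignores any earlier on-treatment values

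*SAP article*

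**What the plan says.** The Safety analyses section of the SAP article works in two layers, both on the safety analysis set.

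- **Descriptive layer.** Every safety outcome is summarised by arm, with a percentage standardised difference for every variable. A difference of 10% or more is treated as meaningful.
- **Model layer.** The section then announces a further step: "In addition, where possible, a linear mixed model or a generalised linear mixed model will be used". Each participant supplies a single response to this model, which is specified "with the safety measure at the end of the trial as the outcome". Arm is the exposure, and the model also takes "the safety measure at the beginning of the trial as a covariate, also accounting for centre variability". Results go into the estimate, interval and p value columns of Table 5. A footnote there makes testing conditional on feasibility.

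The safety analysis set is "all participants who have taken at least one capsule of investigational product or placebo and have at least one subsequent safety assessment". Completing treatment is not required. On outcomes, the SAP states: "The key safety outcome measures are treatment-emergent adverse events and abnormal laboratory analytes". Table 5 gives the rows for treatment-emergent adverse events and treatment-emergent ECG findings the same model columns as QTc, blood pressure, heart rate and weight.

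**The concern.** The safety set admits people who leave early, but the model can use only those who have a final value. The section gives no visit term, no participant-level random effect, no worst or last on-treatment value, and no rule for a participant without an end-of-trial value. It also does not say what counts as the end of the trial for someone who stops early.

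If leaving is related to a safety change, the people lost from the model are those who carry the signal. A rise that occurs on treatment and resolves before the final visit is also invisible to the model. The estimate and interval in Table 5 could then look more reassuring than the on-treatment experience. This matters because the Conclusion says that the results may inform phase 3 trials.

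**Working it through.** **1. Size of the possible omission.** Inputs from the Sample size section: up to 284 screened, up to 50% screen failure, and randomisation "to achieve 120 participants reaching the end of the treatment period in total".

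- Randomised: 284 × (1 − 0.50) = 142 in total. The sentence literally places 142 in each group, which would mean 284 randomised and no screen failures. Only 142 in total agrees with the screening figures.
- Consistency check with an assumed 15% loss: 120 / (1 − 0.15) = 141.2, rounded up to 142.
- Not reaching the end of treatment: 142 − 120 = 22, and 22 / 142 = 15.5%.

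This bounds the number without a final value on the plan's own expectation. It is not a forecast of that number. The Withdrawals/follow up section provides for people who stop the drug but remain in follow-up, and they can have a final value.

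**2. What the model does with a missing final value.** Each participant has one outcome, and the only random effect implied is centre. Someone without that outcome therefore contributes nothing to the arm effect. The resulting estimate is unbiased only if absence of the final value depends on nothing beyond arm, starting value and centre. A change on treatment that led to stopping is not among these.

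The Missing data methods section does not repair this. It sits under the primary analyses, and the Secondary analyses section extends it to secondary outcomes but not to safety. It also imputes nothing when only the outcome is missing.

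**3. Intermediate values.** The Trial design section describes a timeline "which consists of 10 study visits in total". Which safety measures are taken at which visits is in the protocol's schedule, which is not shown. Whatever on-treatment values exist before the final one, the model does not use them.

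**4. Fit to the event rows.** The model needs "the safety measure at the beginning of the trial as a covariate". A treatment-emergent event has no value at the start, and it accrues over the treatment period. For these rows the plan therefore offers either an ill-fitting model or, through its own feasibility conditions, no model.

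**5. Illustration (all figures assumed; none is in the SAP).** Suppose a fraction f of the active arm has a 30 ms QTc rise on treatment, stops and has no final assessment, and nobody else changes.

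| f | Mean on-treatment shift, f × 30 ms | Shift shown by the end-of-trial model |
|---|---|---|
| 10% | 3 ms | 0 ms |
| 15.5% | 4.6 ms | 0 ms |

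The zero follows from the assumptions. If the same people returned with the rise still present, the model would show the full shift. If they returned after it had resolved off drug, it would again show 0 ms.

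**The case against.** The strongest reply is that the model is an addition and not the main safety comparison. The by-arm summaries and standardised differences come first, on a set that does not require completion. The conditions on possibility and feasibility allow treatment-emergent events to be left unmodelled. The detailed definitions of events and laboratory abnormalities are in the protocol and a supplementary table, neither of which is shown. A baseline-adjusted endpoint model also mirrors the primary analysis.

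Most of this stands, and it rules out two stronger readings that a reader might infer:

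- **That early leavers disappear from the safety comparison, so that the safety objective is defeated.** The documents do not support this. The n (%) rows and standardised differences cover the safety set and can show events at any time on treatment.
- **That everyone who stops early is excluded from the model.** This is not established. People who stay in follow-up can be assessed at the end, and any early-termination assessment would be set out in the protocol.

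What the reply does not remove is the rule itself. For continuous measures, where the model can plainly be fitted, it is the only described source of an estimate with an interval, and it is limited to people with a final value.

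**Conclusion.** The point holds for the between-arm models only. They drop safety-set members without an end-of-trial assessment, at most about 22 of 142 (15.5%), and use no earlier on-treatment values. Their form does not suit treatment-emergent events.

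The bound rests on reading the Sample size section as 142 randomised in total, and on taking everyone who does not reach the end of treatment as unassessed. How far any Table 5 estimate would move cannot be derived from the SAP. This is a worthwhile, low-cost improvement to a supplementary analysis and not a failure of the safety reporting as a whole.

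**What to change.** **QTc, blood pressure, heart rate and weight.** Fit a repeated-measures mixed model to all post-baseline on-treatment assessments that the protocol schedules, with arm, visit, arm-by-visit, baseline value, centre and participant. Keep the end-of-trial model as supplementary, and state what counts as the end-of-trial value for participants who stop early.

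**Treatment-emergent adverse events and treatment-emergent ECG findings.** Compare by arm the proportion of the safety set with any occurrence during the treatment-emergent period as the protocol defines it, without a baseline-value covariate.

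**Cost and limits.** The change needs revised wording in the Safety analyses section and a little more programming. The protocol's schedule must first be checked: a measure with only one post-baseline assessment gains nothing from a repeated-measures model. The new model still assumes that missing later values are explained by those observed, but it retains everyone with at least one post-baseline value of the measure.
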